## Methods

### Procedures

We recruited members of the public from a Web-based research panel. Panel members had to be at least aged 18 years and able to read and write German. No other inclusion restrictions were applied.

The participants were first provided with a short introduction to the study and an informed consent sheet. We then collected information on age, sex, and educational degree. Participants were then asked to imagine having tinnitus and having unsuccessfully tried several treatments (see Multimedia Appendix 1). They were then randomly presented with one version of different variations of the research summary on the internet. These contained information on the medical condition and a short summary of evidence for a fictitious new tinnitus medication called *Oroxil* (see Multimedia Appendix 1). After presenting participants with the research summaries, we collected data on different outcomes using a questionnaire developed for the purpose of this study. We asked participants to return to the research summary as needed while answering the questions. At the end of the experiment, participants were asked about their profession (medical or nonmedical) and their history of tinnitus (present or not present). Participants were neither aware of the specific research questions nor of the alternative presentations. The original research summaries were written in German and translated into English for this publication.

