**Q3: Multiple sources of uncertainty**			
	B4	Imprecision (small sample size)	As above
	B42	Publication bias/vested interests and imprecision	Studies indicate that Oroxil may reduce tinnitus. (...) The pros and cons of Oroxil cannot be fully judged, however. The reason for this is that only a small number of people took part in the studies. Furthermore, the company that developed the drug has not published all the studies on Oroxil.
	B432	Publication bias/vested interests and imprecision and indirectness	Studies indicate that Oroxil may ease tinnitus. (...) The pros and cons of Oroxil cannot be fully judged, however. The reason for this is that the studies were small. Furthermore, the people who took part in the studies were exposed to loud noises at work. It is uncertain whether the results also apply to other people. Finally, the company that developed the drug has not published all studies on Oroxil

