Statistical analyses will be conducted in SAS version 9.4 (SAS Institute Inc). All statistical tests will be 2-sided and performed using a 5% significance level. Where applicable, differences in means between groups will be presented together with a 95% CI. All analyses will be conducted on an intention-to-treat basis. Explorative analyses based on potential moderators and mediators are not predetermined.

As we will collect outcome data immediately after the presentation of the research summaries and panel members need to finish the questionnaire to receive an incentive, we have no major concerns regarding missing data. Furthermore, we assume that any dropouts will be likely to be missing at random, as we believe it is unlikely that the intervention has an influence on the responses to the questionnaire. Thus, we do not plan to employ any imputation methods. In case of missing data, we will present this information descriptively.

As the experiment is Web-based and participants come from a panel that provides incentives for participation, there is a risk that some participants only participate to collect their incentive and do not provide valid answers. As a measure of quality assurance, we will exclude data from participants who answer all questions in less than 2 min, spend less than 20 seconds on the page displaying the research summary, and spend less than 1.5 min between reading the research summary and completing the questionnaire (so called speeders). These time limits were determined by a priori test readings. We will also exclude participants who provide all answers in the same column for the matrix questions, that is, when more than 1 item is displayed on the screen (so called straightliners).

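### The plan promises intention-to-treat for all analyses but drops randomised participants for speed and answering pattern recorded after allocation, one limit being a fixed page time for texts of unequal length

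*Protocol article*

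**What the plan says.** In the protocol article, Statistical Analysis, the population for every analysis is fixed in one sentence: "All analyses will be conducted on an intention-to-treat basis".

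The same section then sets a quality filter aimed at panel members who take part only for the incentive. It has three time limits, given as one list joined by 'and':
- Total answering time: "we will exclude data from participants who answer all questions in less than 2 min".
- Page time: a stay of under 20 seconds on the summary screen, with no distinction between versions.
- Time from leaving the summary to the end of the questionnaire: under a minute and a half.

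On the origin of these limits it says only: "These time limits were determined by a priori test readings". A further rule removes straightliners, meaning participants whose answers to matrix questions all fall in one column.

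Data Collection and Allocation Procedure places allocation after the demographic questions and the eligibility check. Procedures places the summary and the outcome questions after that, and adds: "We asked participants to return to the research summary as needed while answering the questions". The only sensitivity analysis described is an ANOVA, which changes the test and not the population.

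Table 1 gives the eight texts. A and B are a single sentence. B432 carries several more, among them "Furthermore, the people who took part in the studies were exposed to loud noises at work".

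**The concern.** Page time, answering time and answering pattern all arise after allocation and after the assigned text has been shown. Dropping people on these grounds is not intention-to-treat, and the section does not say which statement governs the confirmatory Kruskal-Wallis tests.

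The second difficulty is specific to this trial: the intervention is the text. A page-time limit that does not change with text length is easier to breach in a short version than in a long one. A fast reader can fall under 20 seconds in B4 and pass it in B432. If such readers judge effectiveness differently from slower ones, the remaining groups are no longer comparable by randomisation. Straightlining is read from the answers themselves. The multi-item scales for body of evidence and text quality are natural candidates for matrix screens, so that filter may act on secondary outcomes directly.

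**Working it through.** **1. Is the exclusion post-randomisation?** The stated order is demographics, eligibility check, allocation, summary page, outcome questions. All three time limits and the straightliner rule use data from the last two steps. No analysis that retains the excluded participants is named. The contradiction follows without any arithmetic.

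**2. Text lengths.** Counting the English words in Table 1 gives A 7, B 7, B1 22, B4 35, B2 38, B3 50, B42 50, B432 69. Subtracting the 7-word opening sentence leaves these added words: A/B 0, B1 15, B4 28, B2 31, B3 43, B42 43, B432 62.
- Q1: B1 exceeds A and B by 15 words. A and B are equal.
- Q2: the widest gap is B1 to B3, 43 − 15 = 28 words.
- Q3: the widest gap is B4 to B432, 62 − 28 = 34 words. At an assumed 300 to 200 words per minute this is 34/300 × 60 = 6.8 s to 34/200 × 60 = 10.2 s, or 34% to 51% of the 20-second limit.

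**3. Illustrative size, 20-second limit alone.** Assumptions: log-normal reading speed with median 250 words per minute and log-SD 0.4 to 0.6, and a common text of c words (not shown in the article). At the median speed, 20 s covers 250/60 × 20 = 83.3 words. The share excluded is 1 − Φ(ln((c + w)/83.3)/σ), where w is the Table 1 count and σ is the log-SD.

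With c = 150:

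| Version | c + w | σ = 0.4 | σ = 0.6 |
|---|---|---|---|
| A, B | 157 | 5.7% | 14.6% |
| B1 | 172 | 3.5% | 11.4% |
| B4 | 185 | 2.3% | 9.2% |
| B432 | 219 | 0.8% | 5.4% |

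The gaps are 2.2 to 3.2 points for A/B versus B1 and 1.5 to 3.8 points for B4 versus B432. For B1 versus B3 (c + w = 200) the formula gives 2.1 to 4.1 points.

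For A/B versus B1 and B4 versus B432, other text lengths give about 7 to 10 points with c = 100, about 0.3 to 1.7 with c = 200, and below 0.9 with c = 250 to 300.

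**4. Bias.** If those removed differ from those kept by d SD in both arms, the contrast shifts by gap × d. For gaps of 1.5 to 3.8 points and an assumed d of 0.5 to 1, this is 0.015 × 0.5 = 0.0075 to 0.038 × 1 = 0.038 SD, or about 0.01 to 0.04 SD. For scale, the plan's assumed effect is a between-group SD of 0.15 within-group SDs.

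**5. Effect on error.** With 187 per arm the standard error is √(2/187) = 0.103 SD, so the largest shift is 0.038/0.103 = 0.37 standard errors. An unadjusted two-sided 5% test would then reject in 5.1% to 6.6% of cases. The planned pairwise test is Dwass-Steel-Critchlow-Fligner. With its studentized-range limits, and ignoring the overall gate, per-pair error moves from about 1.9% to 2.7% with three groups and from about 1.0% to 1.6% with four.

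**6. The joining word.** Read literally, 'and' means that all three limits must be breached. A page time under 20 s is then necessary but not sufficient. Each arm's exclusion share can only stay the same or fall, and the gap falls with it if answering pace does not itself depend on arm. Someone who breaches the second and third limits has used under 20 + 90 = 110 s on those two parts. The 2-minute limit then adds nothing if its clock starts at the summary page, and little if it also covers the short questions before it. Under 'or', a short page time is enough by itself. The two readings define different analysis sets. The section also does not say whether return visits to the summary count towards page time.

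**7. Sample size.** The plan's own figure reproduces: a one-way ANOVA with four groups, F = 0.15, 5% level and 90% power needs 159 per group (power 0.901). Then 159 × 1.15 = 182.85, so 183. With 1727 randomised, the mean is 1727/8 = 215.9 per arm, and 1 − 183/215.9 = 15% could be lost before falling below 183.

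**The case against.** The strongest defence is that the filter is pre-specified, objective, based on test readings, and aimed at a real threat in a paid panel. That stands as a reason for having the filter and for trusting that it was not chosen from the data. It does not turn the filtered set into an intention-to-treat population, and the article does not say which versions were test-read or that the limits were scaled to length.

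A reader might infer that the fixed limit seriously inflates false-positive findings. A pairwise error of about 16% can be produced, but only by combining a 100-word common text, a full 1 SD outcome difference, the 20-second limit acting alone and an unadjusted test. The documents support none of these, and the last two depart from the rule and the test as written. Participants also read German, whereas the counts are English. Nor do the documents show that the filter does remove different kinds of reader from each arm. They show that it can.

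A reader might also think that a limit scaled to words per second would solve the problem. It would lessen the dependence on length, but it remains a post-randomisation exclusion and does not restore intention-to-treat.

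**Conclusion.** The contradiction holds as written and needs no assumption: the intention-to-treat statement and the exclusions cannot both define the confirmatory population. That the page limit can make exclusion depend on arm follows from Table 1 for Q2, Q3 and B1 versus A/B. Length cannot affect A versus B.

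The size of any bias is not established. The c = 150 figures in the working are an illustration of the 20-second limit alone and rest on assumed reading speed, spread, common text length and outcome difference. With a longer text or a literal 'and', the bias could be negligible. The case for change rests on the contradictory population and the direction of the dependence, not on a demonstrated error rate.

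**What to change.** - Run the confirmatory Kruskal-Wallis and Dwass-Steel-Critchlow-Fligner analyses on all randomised participants with outcome data, in their assigned arm. Make the quality-filtered set, with speeders and straightliners removed, a named sensitivity analysis.
- If the filtered set is to stay primary, drop the intention-to-treat label for it and add the all-randomised analysis as a named sensitivity analysis.
- State whether the three time limits are joined by 'and' or 'or', and whether return visits count towards page time.
- Report exclusions by arm and by reason.

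Data collection is complete, so this means a documented change to the analysis and one further run on data already held. The price is that inattentive responders stay in the primary set and may dilute differences, by an amount the documents do not allow one to estimate. About 216 per arm against the 183 from the plan's four-group calculation leaves some margin for that.

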### Sample Size Calculation

We based the sample size calculations for all 3 research questions on the following considerations and assumptions. We used the comparison of 4 groups (which corresponds to the second study question) as a basis and proceeded from a 1-way ANOVA with equal sample sizes in each group. We assumed a significance level of 5% and a statistical power of 90%. We decided to assume an effect size of *F*=0.15 for the primary outcome (confirmatory analysis), where *F* denotes the ratio of the SD of the group means and the common SD within each group. This decision was made based on a pretest of 2 of the research summaries, where we found small effect sizes in the range of up to *F*=0.3, depending on the outcome variable. According to Cohen, the chosen value of *F* lies between a small (*F*=0.10) and a medium (*F*=0.25) effect size [19]. Sample size calculations were conducted with nQuery version 3.0 (Statistical Solutions Ltd). This resulted in a number of 159 participants in each group. As the primary analysis is a nonparametric test, we added 15% according to a general rule of thumb [20]. To allow some leeway, we decided to randomize a total of 1500 participants, equaling an average of 187.5 participants per group.

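### The 90% power claimed for all three questions was computed for four groups only; the three-group questions Q1 and Q3 have about 85% by the plan's own method

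*Protocol article*

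**What the plan says.** The Sample Size Calculation section of the protocol article begins "We based the sample size calculations for all 3 research questions on the following considerations and assumptions". It then narrows the calculation: "We used the comparison of 4 groups (which corresponds to the second study question) as a basis". The inputs are a one-way ANOVA with equal groups, a 5% level, 90% power and F=0.15 for the primary outcome, "where *F* denotes the ratio of the SD of the group means and the common SD within each group". The result is given as "This resulted in a number of 159 participants in each group". The authors add 15% because the primary analysis is nonparametric, and finish with "To allow some leeway, we decided to randomize a total of 1500 participants, equaling an average of 187.5 participants per group".

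No other group count, effect size or power appears. Under Interventions and in Table 1, Q1 compares three versions (A, B, B1), Q2 compares four (B1 to B4) and Q3 compares three (B4, B42, B432). Under Statistical Analysis, each question has its own confirmatory Kruskal-Wallis test, and "All statistical tests will be 2-sided and performed using a 5% significance level".

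**The concern.** Sizing the trial on the question with the most groups looks cautious, but at a fixed F it is the reverse. The noncentrality of the ANOVA F test is F² times the total number of participants in that comparison, so a comparison with one group fewer, each of the same size, carries less information. The numerator degrees of freedom fall from 3 to 2, which recovers part of the loss but not all of it. The three-group questions therefore set the required group size, and they were not calculated.

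Two of the three confirmatory questions are thus presented with a power the design does not give them. The practical risk lies in interpretation: a non-significant result for degree of uncertainty (Q1) or for additive effects (Q3) would be taken as better supported than it is. Type I error is not affected.

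**Working it through.** **Inputs.** From Sample Size Calculation: α = 0.05, target power 0.90, F = 0.15, 159 per group, a 15% addition, and 1500 planned (187.5 per group). From Interventions and Table 1: k = 3 groups for Q1 and Q3, k = 4 for Q2. From Results: 1727 randomised, or 1727/8 = 215.9 per group.

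**Formula.** For k groups of n, the noncentrality is λ = k × n × F². Power is the probability that a noncentral F variable with k−1 and k(n−1) degrees of freedom and noncentrality λ exceeds the central 95% point. The omnibus F test has one rejection region, so the two-sided convention changes nothing.

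**Step 1: reproduce the plan's figure (k = 4).**
- n = 158: power 0.8991.
- n = 159: λ = 4 × 159 × 0.0225 = 14.31, power 0.9011.

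The smallest n reaching 90% is 159, an exact match. Defining F with a k−1 divisor would give 211, so that is not what was used.

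**Step 2: same method, k = 3.**
- n = 159: λ = 3 × 159 × 0.0225 = 10.73, power 0.841.
- n = 189: λ = 3 × 189 × 0.0225 = 12.76, power 0.901. This is the smallest n reaching 90%.
- With the 15% addition: 189 × 1.15 = 217.35, rounded up to 218; 218 × 8 = 1744 (unrounded, 217.35 × 8 = 1739).

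For comparison, the four-group figure gives 159 × 1.15 = 182.85, rounded up to 183; 183 × 8 = 1464. The leeway in 1500 is therefore 36 people (36/1500 = 2.4%).

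**Step 3: power at the planned and the actual size.** Dividing the group size by 1.15 applies the plan's allowance for the nonparametric test.

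| Basis | n used per group | Q1, Q3 (k=3) | Q2 (k=4) |
|---|---|---|---|
| Calculated n | 159 | 84.1% | 90.1% |
| 1500, with allowance | 187.5/1.15 = 163.0 | 85.0% | 90.9% |
| 1500, no allowance | 187.5 | 89.8% | 94.5% |
| 1727, with allowance | 215.9/1.15 = 187.7 | 89.9% | 94.5% |
| 1727, no allowance | 215.9 | 93.7% | 97.1% |

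At 163.0 per group, a three-group comparison reaches 90% power at F = 0.161, not 0.15. A simulated Kruskal-Wallis test with three groups, about 187.5 per group and a five-category outcome (distribution assumed) gave 88–89%.

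**Step 4: effect of the planned exclusions.** Statistical Analysis removes speeders and straightliners but gives no expected rate, so the rates below are assumptions. All figures include the allowance.

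| Excluded (assumed) | 1500: Q1, Q3 | 1500: Q2 | 1727: Q1, Q3 | 1727: Q2 |
|---|---|---|---|---|
| 5% | 83.1% | 89.3% | 88.2% | 93.4% |
| 10% | 80.9% | 87.4% | 86.4% | 91.9% |
| 15% | 78.4% | 85.3% | 84.2% | 90.2% |

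**The case against.** Four arguments can be made for the plan.

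**The basis is disclosed.** The section says openly that it used the four-group comparison, and 159 is right for it. That is so, and nothing is hidden. But the same paragraph applies the result to all three questions and gives no lower figure for Q1 and Q3.

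**F need not be constant across group counts.** If the largest difference between means is held at the value that gives F=0.15 with four groups, the three-group F changes. At 159 per group, the power for three groups is then:
- two extremes with the rest midway: F=0.173, 93.2%;
- evenly spaced means: F=0.164, 90.3%;
- one group differing: F=0.163, 90.0%;
- an even split of the four groups, becoming one against two: F=0.141, 79.3%.

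On that assumption the four-group basis is adequate in three of the four patterns. The plan, however, makes no such assumption. It names one F for the primary outcome and applies it to every question, so its power claim has to be judged on that F.

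**The 15% is only a rule of thumb.** Without it, power is 89.8%, and the direct simulation gives 88–89%. This is the strongest point on size: the real loss may be only 1 to 2 percentage points. But the plan itself treats the allowance as needed, and even without it the three-group power stays just under 90%.

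**Enrolment went beyond 1500.** With 1727 randomised, Q1 and Q3 reach 89.9% with the allowance. This largely repairs the trial as run, but only before exclusions, and it does not correct the planned figure.

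**Conclusion.** The point holds. The 90% power at F=0.15 was derived for Q2 and does not carry over to Q1 and Q3. By the plan's own method, the planned 1500 gives those two questions 85.0%, so the type II error is about 15% where 10% is claimed. The gap is about 5 points with the full nonparametric allowance and no more than 2 without it. At 1727 it is close to nil before exclusions.

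The conclusion rests on F=0.15 for every question, equal group sizes, and the 15% allowance read as a real loss of efficiency. The first two are the plan's own statements, and the third follows from its reason for adding the 15%. The figures net of exclusions also depend on assumed rates. The error does not undermine the design or the analysis. It is a wrong statement of power for two of the three confirmatory questions.

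**What to change.** Correct the Sample Size Calculation section in three respects:

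1. State that 159 per group, and 90% power at F=0.15, apply to the four-group question Q2.
2. State that at 1500 participants, with the 15% allowance, Q1 and Q3 have about 85% power at F=0.15, or 90% at F=0.161.
3. When reporting, give the power of each question for the numbers actually analysed, after speeders and straightliners are removed, in place of a single 90%.

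This is a change of text only. It needs no extra participants, no new data and no change to any test. The one cost is a less favourable stated power for two questions.

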### Data Collection and Allocation Procedure

The data collection was run by the Survey Centre Bonn (uzbonn—Gesellschaft für empirische Sozialforschung und Evaluation), a spinout company of the Center for Evaluation and Methods at the University of Bonn. UNICOM Intelligence (formerly IBM SPSS Data Collection) was used for data collection (UNICOM Systems, Inc). This software uses Microsoft’s .NET Framework 4.0 random generator to generate random numbers to allocate the participants to the research summaries. A quota was used to ensure equal representation of different age groups and sexes. Once a quota cell was full, enrollment for this quota was closed. Thus, allocation happened after panel members answered demographic questions and were computer-checked for eligibility. As the experiment was entirely Web-based, the allocation sequence was concealed from investigators and data collectors. The data analyses will be conducted by a statistician from the Medical Biometry Department at IQWiG.

### Ethics and Dissemination

The study was presented to the ethics committee at the University of Erfurt (EV-20180921). The committee decided that the research was exempt from the requirement of ethical approval because of its negligible risk to participants and as only nonidentifiable data were collected. The study results will be disseminated via publication and conference presentations.

## Results

The trial was set up between February and April 2018. Data collection was completed in May 2018. Recruitment and data collection were Web-based. First, a website, only accessible via a link available to invited panel members, was set up (password protected site). Font and color use matched the appearance of the national German consumer health website [7]. Then, 6 of the authors ([name]) read and reread the recruitment texts and the research summaries. The same authors also tested the questionnaire used for data collection. After 2 rounds of debugging, the website and questionnaire were finalized and data collection was started.

Participants were recruited by the Survey Centre Bonn from a Web-based panel of members of the German public. The panel was provided by the online access panel provider Bilendi. Participation was only permitted with use of a desktop computer.

Participants were first informed about the general purpose of the study (to study the perception of health information), the duration required for answering the questionnaire, and the use of data. Only anonymous data were collected. The outcome data were collected over 10 consecutive screens. Participants were able to move forward and backward between the screens. However, once they completed the data collection for the primary and secondary outcomes, moving backward to that section of the questionnaire was not possible anymore. The order of items in the multiitem outcomes was presented in random order. We used soft reminders to encourage participants to answer all questions, that is, the participants were asked to complete unanswered questions before proceeding but were not obliged to answer them. The only mandatory questions were regarding age and sex, as this information was needed to check eligibility. Repeated participation by the same panel member was prevented by the use of a password encrypted access link, which was provided to participants via email.

In total, 2099 invited panel members were assessed for eligibility and 1727 were randomized to 1 of the 8 groups.

